## Abstract

**Background:**

Cardiological complications of oncological treatment, including the most serious one, heart failure, constitute a significant and still unsolved clinical problem. A history of dyslipidemia and complications of atherosclerosis, including coronary artery disease, are established risk factors for cardiotoxicity in cancer patients. In recent years, a protective effect of statin treatment on the development of heart failure in cancer patients has been observed. This protocol describes a study aiming to assess the prognostic value of coronary atherosclerosis burden and the CAC score on the onset of cardiac dysfunction associated with cancer therapy.

**Methods:**

ANTEC (Atherosclerosis iN chemoTherapy-rElated Cardiotoxicity) is a single-site, prospective, observational study to evaluate the influence of the coronary atherosclerosis and CAC score assessed by computed tomography on the development of left ventricular systolic dysfunction in cancer patients with at least moderate cardiotoxicity risk. A group of 80 patients diagnosed with cancer prior to high-dose anthracycline chemotherapy (doxorubicin ≥ 240 mg / m2 body weight or epirubicin ≥ 600 mg / m2 body weight), without a history of heart failure and coronary artery disease, will be included in the study. Patient follow-up is planned for 12 months. In all patients, coronary computed tomographic angiography (CCTA) will be performed once at the beginning of the study. The primary endpoint is the onset of cancer therapy-related cardiovascular toxicity, defined as mild, moderate, severe and very severe according to ESC 2022 Cardio-oncology guidelines. During follow up, echocardiography with GLS assessment will be performed every three months. Additionally, new biomarkers of atherosclerosis (IL-6, MPO, TNF-alpha) will be measured every 6 months. The study registration identifier on clinicaltrials.gov is NCT05118178.

**Clinical trials registry:**

This study is listed on cinicaltrials.gov with identifier NCT05118178.

## 1. Background

Cancer mortality has decreased significantly over the last years due to the earlier diagnosis and increasing efficiency of chemotherapy. The benefits of administering anti-cancer drugs are to some extend limited by their adverse effects on the cardiovascular system [1–4]. The most serious cardiotoxic effect of chemotherapy is damage to the heart muscle, leading to heart failure. Cardiotoxicity is particularly important in the context of anthracycline use. The main mechanism of anthracycline cardiotoxicity is direct myocardial cell damage [5–9].

In addition, studies have shown that oncological treatment, including anthracyclines, accelerates the development of atherosclerosis and its complications [1–4]. The mechanisms by which chemotherapy with anthracyclines may causes or promote premature atherosclerosis are multifactorial. Both endothelial damage as well as arterial thrombosis, microcirculation damage and long-term changes in lipid metabolism have been reported [10–13]. However, the impact of asymptomatic atherosclerotic lesions on the occurrence of heart muscle damage in the course of chemotherapy is still an open question and currently CT angiography or CAC scoring is not routinely performed.

Risk factors for cardiotoxicity include older age, arterial hypertension, diabetes, dyslipidemia, obesity and smoking, and they coincide with atherosclerosis risk factors [1]. Several, mainly retrospective, studies with statins in the prevention of heart failure have been published, but the mechanism of their cardioprotective effect is still unknown [14–23].

Studies that define the contribution of pre-existing coronary atherosclerosis and/or its progression to toxicity during anthracycline treatment are lacking. We therefore designed our study to define both cardiac function, by echocardiogram, and coronary atherosclerosis and calcification by CCTA, at baseline and at intervals in a cohort receiving anthracycline chemotherapy.

### 1.1 Study aims

Assessment of the prognostic value of the coronary atherosclerosis and the CAC score before chemotherapy for the occurrence of the cardiovascular toxicityEvaluation of IL-6, MPO and TNF-alpha for use in the diagnosis of cardiotoxicity during oncological treatment.Influence of studied parameters, i.e. presence of atherosclerosis, echocardiographic parameters and biomarker levels on the prognosis of patients undergoing cardiotoxic chemotherapy

## 2. Methods

### 2.1 Study structure

The ANTEC Trial is a single-center, prospective, observational trial evaluating the impact of atherosclerosis in the coronary arteries determined by computed tomography on the risk of cardiotoxicity related to anthracycline-based chemotherapy. The trial is being carried out in accordance with the principles of the Declaration of Helsinki and the International Conference on Harmonization Good Clinical Practice guidelines. The conduct of the study is approved by an Independent Ethics Committee at the Maria Sklodowska-Curie National Research Institute of Oncology in Warsaw (the date of approval– 28 October 2021, approval no. 80/2021) and all participants will provide written informed consent before study entry. The registration identifier on clinicaltrials.gov is NCT05118178.

### 2.2 Study patients

The study will include patients with cancer, diagnosed and qualified for further systemic treatment with high-dose anthracycline chemotherapy at the Maria Sklodowska-Curie National Research Institute of Oncology in Warsaw. Patients must give informed and voluntary consent to participate in the study and meet all the inclusion criteria and none of the exclusion criteria listed in Table 1.

**Table 1 pone.0288146.t001:** Inclusion and exclusion criteria.

Inclusion criteria
1. Eastern Cooperative Oncology Group (ECOG) performance status from 0 to 2.
2. Age ≥18 years at the time of signing the informed consent.
3. Known neoplastic disease prior to the initiation of chemotherapy with a high dose of anthracyclines (doxorubicin ≥ 240 mg / m2 b.w. or epirubicin ≥ 600 mg / m2 b.w.)
4. No history of heart failure (left ventricular ejection fraction ≥ 50% as assessed by echocardiography).
5. No history of: coronary artery disease, stroke and lower limb atherosclerosis
6. At least moderate baseline cardiovascular toxicity risk according to Heart Failure Association–International Cardio-Oncology Society stratification [1]
Exclusion criteria
1. History of heart failure and/or left ventricle ejection fraction <50%
2. Significant valvular heart disease
3. Previous chemotherapy or radiation to the chest
4. Presence of any disease with a life expectancy <1 year in the opinion of the investigator.
5. Drug or alcohol abuse
6. Lack of possibility or contraindications for computed tomography (CT) scan.

### 2.3 Study visits and follow up

Approximately 80 patients are planned to be included in the study. Each patient will have 5 program visits every 3 months for 12 months. At the first visit, the patient will be informed about the type of the proposed follow-up, its course and planned tests. After signing the consent to participate in the study, patients will undergo planned procedures according to the schedule shown in Table 2.

**Table 2 pone.0288146.t002:** Schedule of Activities (SoA).

Visit	1	2	3	4	5
Days from first Visit window	1	90 (±14)	180 (±14)	270 (±14)	360 (±14)
Informed Consent	x				
In-/exclusion criteria	X				
Medical History/ Concomitant diagnoses	x				
Demographics	x				
NYHA classification	X	X	X	X	X
ECOG performance status	X	X	X	X	X
Physical exam	X	X	X	X	X
Concomitant Therapy	X	X	X	X	X
Assessment of Endpoints		X	X	X	X
12-lead-ECG	X	X	x	X	x
Echocardiography with GLS assessment	x	X	X	X	X
Lab test	x	X	X	X	X
CCTA	x				
IL-6, MPO, TNF-alpha	x		x		x

**Abbreviations**: ECG = electrocardiogram; ECOG = Eastern Cooperative Oncology Group; GLS = global longitudinal strain; NYHA = New York Heart Association; CCTA = Coronary Computed Tomographic Angiography

Clinical variables such as: age, gender, cardiovascular risk factors (hypertension, diabetes, hyperlipidemia, obesity, smoking status), alcohol use, previous medical history, concomitant heart failure therapy, statins or other lipid lowering medications will be documented at baseline and then checked at each visit. Lipid levels and diabetes status at each visit will be determined using a fasting blood sample and lipid panel at that visit.

Cancer diagnosis and current treatment (including cumulative dose of anthracyclines) will be collected and documented at each visit.

In all patients, a single coronary computed tomographic angiography (CCTA) will be performed at the beginning of the study, with calculation of coronary artery calcium (CAC) score according to the Agatston method. Contrast cardiac CT scanning for CAC quantification will be performed with a 64-slice CT scanner (Revolution Evo, GE Healthcare, Waukesha, USA) with prospective ECG triggering. A tube voltage of 120kVp will be used. Images will be reconstructed with a slice thickness of 0.625 mm and CACS was quantified using the Agatston method with dedicated software by a well-trained researcher.

At each visit, transthoracic echocardiography will be performed by using a Philips EPIQ Elite instrument (Philips Healthcare, Andover, Massachusetts). The following echocardiographic parameters will bez assessed: left atrium diameter, interventricular septum diameter, posterior wall thickness, left ventricle (LV) end-diastolic diameter, LV end-systolic diameter, LV ejection fraction, and mitral inflow with the use of Doppler echocardiography. Diastolic function will be evaluated by mitral inflow E/A pattern, E/A ratio, annular tissue Doppler curves and E/E’ ratio. Images will be digitally stored for offline analysis on custom software (Q-Station, Philips Healthcare, Andover, Massachusetts). Left ventricular, two-dimensional peak systolic global longitudinal strain (GLS) will be analysed by an offline semi-automated speckle tracking imaging technique from the three standard apical views. Analyses will be performed by one board-certified physician, who will be blinded to all clinical characteristics.

Blood samples will be collected et each visit and analyzed by the central laboratory (The Maria Sklodowska-Curie National Research Institute of Oncology). Laboratory tests will include: alkaline phosphatase, alanine aminotransferase (ALT), aspartate aminotransferase (AST), urea, creatinine, glucose, magnesium, potassium, sodium, uric acid, morphology, glycated hemoglobin, lipid profile, d-dimers, fibrinogen and hs-CRP.

Blood samples to determine plasma levels of high-sensitivity troponin T (hs-cTnT) and N-terminal natriuretic pro-peptide (NTproBNP) will be processed in a central laboratory using standardized methods. New atherosclerosis biomarkers (IL-6, MPO, TNF-alpha) will be assessed every 6 months using Quantikine ELISA kit R&D Systems, Inc., USA & Canada.

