#### 2.4.2 Secondary endpoints

The secondary composite endpoint include: time to all-cause death, cardiovascular death, myocardial infarction, and stroke.

Other secondary endpoints include: (1) the severity of atherosclerosis in the coronary arteries and the calcification index in computed tomography, (2) the percentage decrease in left ventricular ejection fraction and GLS in echocardiography, (3) changes in the concentration of biomarkers involved in inflammatory and atherosclerotic processes.

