### 3.2 Sample size calculations and statistical analysis

The estimated group size was determined for the one-sided Pearson chi-square test for two proportions. We considered an alternative hypothesis of an approximately 2-fold increase in the incidence of cardiotoxicity with the presence of atherosclerotic lesions versus null hypothesis of no effect of atherosclerotic lesions. In particular, we assumed that the incidence of cardiotoxicity in the population with and without atherosclerotic lesions will vary from 60% to 75% and from 30% to 40% respectively and that the atherosclerotic lesions of various severity will be present in 30% to 40% of patients. With additional standard assumptions of 0.05 statistical significance and 80% power and assuming the estimated sample size varies from 54 to 80 individuals, thus the desired sample size of 80 was established.

Handling of missing data will depend on the proportion of cases affected by missing values. Complete case analysis will be performed if any missing values occur in less than 5% of cases. Otherwise, imputation through full conditional specification (FCS) methods are planned, accounting for the model of interest.

Statistical analysis of the results obtained in this trial will focus on the comparison of groups determined on the basis of the presence of atherosclerotic lesions, and will include a comparison of the characteristics of these groups using for comparisons of numerical variables, the Wilcoxon test, and for categorical variables the Fisher or chi-square tests. The Cochran-Armitage test on the existence of a trend for an ordinal scale variable will be used to assess the effect of the severity of atherosclerotic lesions on the incidence of cardiotoxicity.

Cumulative incidence of cancer therapy-related cardiovascular toxicity (primary endpoint) will be estimated using competing risk approach with death from other causes as the competing event. Fine and Gray’s proportional subhazards model will be used to estimate incidence by group and evaluate the impact of atherosclerotic lesions controlling for potential confounders. This model may be used in combination with missing data imputation, if necessary, with substantive model compatible fully conditional specification (SMC-FCS) imputation [24].

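### As written, the Agatston calcium score comes from a contrast CT reconstructed at 0.625 mm, which does not give a valid Agatston score; the lesion-based analyses and N = 80 are not affected

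*Protocol article*

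**What the plan says.** Section 2.3 (Study visits and follow up) plans one CT examination per patient: "a single coronary computed tomographic angiography (CCTA) will be performed at the beginning of the study". The same sentence names Agatston scoring as the way the calcium score is obtained. The acquisition is then described: "Contrast cardiac CT scanning for CAC quantification will be performed with a 64-slice CT scanner". The tube voltage follows ("A tube voltage of 120kVp will be used"), and then the reconstruction and scoring: "Images will be reconstructed with a slice thickness of 0.625 mm and CACS was quantified using the Agatston method".

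Table 2 lists CCTA at visit 1 and no other CT. The article mentions no unenhanced series, no thicker reconstruction, no adapted attenuation threshold and no conversion to a standard score.

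The calcium score has two roles. It is an exposure in the first aim (section 1.1): "Assessment of the prognostic value of the coronary atherosclerosis and the CAC score before chemotherapy". It also appears among the other secondary endpoints (section 2.4.2): "the severity of atherosclerosis in the coronary arteries and the calcification index in computed tomography". The statistical section (3.2) rests on something else, a "comparison of groups determined on the basis of the presence of atherosclerotic lesions".

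**The concern.** The Agatston score is defined by how it is measured. Within each slice, the area above a fixed attenuation threshold is weighted by peak density, and the results are summed over slices. The threshold identifies calcium only if nothing else in the coronary artery exceeds it, which is why the method belongs to unenhanced images. Slice thickness is also part of the definition, because the number of slices and the image noise both change the sum.

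Section 2.3 attaches two settings to calcium scoring, contrast and 0.625 mm, and neither fits the method it names. This is a positive specification that conflicts with its own label, not a detail that a short article has left out.

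What is at stake is the calcium-score half of the first aim and the calcification index. If the text were followed literally, a patient without coronary calcium could receive a score above zero. The results could not be set beside the earlier calcium-score studies reviewed in the Discussion. Because CT is done once, before chemotherapy, a patient without an unenhanced series cannot be given a valid pre-treatment score later.

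**Working it through.** **1. The passages side by side.**

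| Item | Section 2.3 as written | What the named method requires |
|---|---|---|
| Scan used for calcium scoring | Contrast | Unenhanced |
| Slice thickness | 0.625 mm | About 2.5 to 3 mm (assumption, not in the document) |
| Threshold | Not stated | Fixed, 130 HU (assumption, not in the document) |
| Tube voltage | 120 kVp | Not in dispute |

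**2. Does opacified lumen pass the threshold?** The document gives no attenuation values. Assume a contrast-filled lumen of 300 to 500 HU and a threshold of 130 HU.

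- Lower end: 300 / 130 = 2.3
- Upper end: 500 / 130 = 3.8

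The conclusion does not need these exact values. It holds wherever the opacified lumen exceeds the threshold. Raising the threshold above the lumen would avoid the problem, but the result would no longer be an Agatston score.

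**3. Slice thickness.** Against the assumed 2.5 to 3 mm, 0.625 mm gives 2.5 / 0.625 = 4 to 3 / 0.625 = 4.8 times as many slices over the same length, each with more noise. This is a second departure from the definition, independent of contrast.

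**4. Which analyses use the score?** Going through section 3:

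- Sample size: presence of atherosclerotic lesions.
- Group comparison: presence of lesions.
- Cochran-Armitage trend test: severity of lesions.
- Fine and Gray model: lesions, with adjustment for confounders.
- Repeated-measures ANOVA: lesion status.

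None names the calcium score. Presence and severity of lesions can be read from a contrast angiogram, for which contrast and thin slices are appropriate.

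**5. Is N = 80 affected?** The plan's figure is reproduced from lesion inputs alone. Inputs from section 3.2: 60% with lesions, 30% without, lesion prevalence 30%, one-sided alpha 0.05, power 80%. Allocation ratio k = 0.70 / 0.30 = 2.333. Pooled proportion = 0.30 × 0.60 + 0.70 × 0.30 = 0.39.

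n₁ = [1.645 × √((1 + 1/k) × 0.39 × 0.61) + 0.842 × √(0.60 × 0.40 + 0.30 × 0.70 / k)]² / (0.60 − 0.30)²

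= [1.645 × 0.583 + 0.842 × 0.574]² / 0.09 ≈ 23.1, rounded up to 24.

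n₂ = 24 × 2.333 = 56, and 24 + 56 = 80. This matches the upper end of the stated range of 54 to 80. No calcium-score input enters, so changing the imaging text leaves N as it is.

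**The case against.** The strongest reply is that this is a drafting slip. The word for contrast may stand where its opposite was meant, and 0.625 mm may be the angiogram's reconstruction carried into the calcium sentence. The tense changes within that sentence, which suggests loosely merged text. Section 3.1 says measurements follow routine practice and that CCTA is reviewed by a trained team member. A score that counted every opacified segment would be visibly wrong to the trained researcher named in section 2.3. The full protocol or an imaging manual, not shown here, may describe an unenhanced series. The definition of the Agatston method is also not in the document.

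Much of this stands. The article does not prove that patients are being scored wrongly, and its silence about an unenhanced series is weak evidence that none exists. But both unsuitable settings are explicitly assigned to calcium scoring, and nothing elsewhere corrects them. The argument uses only the definition of the method that the protocol names, with the numerical values marked as assumptions. If the cause is a slip, the text still needs correcting.

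Three stronger readings are tempting, and the document does not support them.

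- *The main comparison is compromised or loses power.* It uses lesions, not the calcium score. Power losses calculated for a misclassified binary lesion variable would concern an exposure that this problem does not touch.
- *The association is pulled toward the null.* Counting lumen as calcium is a systematic error that could vary with vessel size and opacification. Its direction is not determined.
- *A planned analysis by published calcium categories fails.* The Discussion reviews earlier calcium-score studies, but no such analysis is planned in section 3.

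**Conclusion.** The point holds in a limited form. Followed literally, section 2.3 yields a number that is not a valid Agatston score, because of the contrast and, separately, because of the thin slices. The consequence is confined to the calcium-score part of the first aim and the calcification index in section 2.4.2. The lesion-based comparison, the trend test and N = 80 stand.

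The conclusion rests on the standard definition of the method. The figures of 130 HU, 300 to 500 HU and 2.5 to 3 mm are assumptions, and the argument would survive moderate changes in each. Neither the size nor the direction of the error in any association can be derived from the document. Whether the text reports actual practice or a merged description also cannot be settled from it. The text should be corrected under either reading.

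**What to change.** Rewrite the CT paragraph in section 2.3 so that each measurement is tied to its own series:

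- **Agatston score:** taken from the unenhanced, ECG-triggered series of the same session, with the reconstruction thickness for which the score is defined stated in the text.
- **Lesion presence and severity:** taken from the 0.625 mm contrast series.

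If no unenhanced series is acquired, for all patients or for some, do not report an Agatston score for them. Use plaque measures from the angiogram, or a contrast-based calcium measure that is named and justified as such. Align the wording on the calcium score in sections 1.1 and 2.4.2 with whichever applies.

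The cost is a wording correction, plus a re-reconstruction where an unenhanced series exists but was reconstructed at the wrong thickness. The real downside is the possible loss of the Agatston score for patients without an unenhanced series. No additional scan is asked for, and the primary analysis and sample size do not change.

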### 2.4 Primary and secondary endpoints

#### 2.4.1 Primary endpoint

The primary endpoint is the onset of chemotherapy-related cardiac dysfunction defined as either mild, moderate, severe or very severe according to ESC 2022 Cardio-oncology guidelines [1].

#### 2.4.2 Secondary endpoints

The secondary composite endpoint include: time to all-cause death, cardiovascular death, myocardial infarction, and stroke.

Other secondary endpoints include: (1) the severity of atherosclerosis in the coronary arteries and the calcification index in computed tomography, (2) the percentage decrease in left ventricular ejection fraction and GLS in echocardiography, (3) changes in the concentration of biomarkers involved in inflammatory and atherosclerotic processes.

## 3. Data acquisition and statistical analysis

### 3.1 Data acquisition and quality control

All measurement will be performed according to routine diagnostic standards. The critical measurements (CCTA, ECHO) will be reviewed and coded by a trained member of the study team to ensure comparability of the results. Electronic case report forms (eCRFs) will be developed to capture the study subject data in secure internal environment. The clinical data will be entered manually and laboratory data will be extracted from the Hospital Information System (HIS). The data will be pseudonimised using study subject identification number, with the list of linking these numbers to the patient identification number used in the HIS stored separately. To ensure data quality validation rules will be implemented in eCRFs to preclude entry of inconsistent or out-of-range values. Data will be assessed periodically to identify missing and outlying values to be verified with the medical notes available in HIS by the study team.

